## Abstract

**Background:**

Goal-Oriented Cognitive Rehabilitation (GREAT-CR) is an evidence-based early intervention for people with mild-moderate dementia that improves goal attainment and functional outcomes. In Ireland, this intervention is not widely available, likely due to resource shortages within memory services. This project aims to pilot and evaluate a new service delivery model for GREAT-CR, and to assess its impact on goal attainment, cognition, and quality of life for people living with dementia.

**Methods:**

This pilot study implements a new service-delivery model where trainee psychologists will offer GREAT-CR within Memory Clinics in Ireland. Sub-study 1 will evaluate the impact of GREAT-CR in this context and sub-study 2 will evaluate the implementation model. Sub-study 1 will employ a quantitative pre-post design with an embedded randomized *N*-of-1 experimental design. Outcomes will include goal attainment, quality of life, and cognitive function. A subset of three participants will be randomly selected for an *N*-of-1, single-case experimental design evaluation. The *N*-of-1 design will include within-case and start-point randomization. Sub-study 2 will include a mixed-methods approach to evaluate the feasibility, acceptability, appropriateness, and potential sustainability of the implementation model at organizational, practitioner, and service-user levels. We will conduct semi-structured interviews with key stakeholders and analyze the data using framework analysis. Quantitative implementation outcomes will be assessed against predefined targets to support qualitative findings.

**Discussion:**

The results will inform guidelines for wider service delivery. This project aims to ensure immediate and long-term impacts for participants with early-stage dementia and their carers by increasing opportunities to access evidence-based psychosocial interventions; for trainee psychologists by creating novel placement opportunities; and for service providers by disseminating GREAT-CR implementation recommendations. By addressing current staffing and resource limitations, this model has the potential to enhance the availability of GREAT-CR for dementia patients in Ireland.

## Background

People living with dementia (PLwD) can retain their abilities, learn new skills, and improve their brain health [1]. Those with a diagnosis of dementia should be empowered to access interventions that can maximize independence and everyday function, improve quality of life, and prevent excess disability. Cognitive rehabilitation is an evidence-based intervention for supporting PLwD to achieve their goals by maintaining or enhancing cognitive and everyday function [2,3]. Although variations in approaches to general cognitive rehabilitation exist (e.g.,[4]), we refer to Linda Clare’s Goal-Oriented Cognitive Rehabilitation (GREAT-CR) [5]. Research has shown that GREAT-CR has a positive impact on the lives of PLwD, and is a cost-effective intervention [6]. Evidence from single-case [7] and small-group intervention studies, along with randomized controlled trials (RCT) [5,8,9] indicates that GREAT-CR holds promise in enhancing goal attainment, well-being, and engagement in daily activities among individuals with mild cognitive impairment (MCI) and early-stage dementia [10]. GREAT-CR also shows potential in enhancing caregivers’ self-reported quality of life [11]. The National Institute for Health and Clinical Excellence Guidelines [12], the World Alzheimer Report [13] and the Health Service Executive’s (HSE) Model of Care for Dementia in Ireland [14] have recommended that GREAT-CR should be available to people with a diagnosis of dementia.

Irish PLwD have been advocating for their right to access early evidence-based interventions for many years. In 2013, a roundtable discussion with PLwD and their family members highlighted the importance of accessing early interventions that help the person with dementia to remain at home for longer [15]. Subsequently, the National Dementia Strategy [16] identified timely diagnosis and intervention as a “priority action area”. Despite this, over ten years later there remains a treatment gap where evidence-based early interventions do not routinely follow diagnosis. Barriers to the implementation of psychosocial interventions in healthcare settings often include limited staff time and capacity, meaning that memory services may be motivated to deliver GREAT-CR but may lack the capacity to do so.

Our project aims to address implementation barriers by offering an innovative solution to resourcing issues. We aim to create a new service model for the delivery of community-based GREAT-CR, through a supervised placement program for early-career psychologists. In Ireland, masters/doctoral level psychologists are required to complete supervised clinical placements as part of their training, but the demand for placements in older adult services is often unmet. We aim to alleviate this unmet need by creating a placement model within Irish Memory Clinics where trainee psychologists receive training and supervision to deliver GREAT-CR to PLwD in the community.

Our research proposes a two-phase approach to evaluating this implementation model. First, we will evaluate the impact of GREAT-CR on goal attainment, quality of life and cognitive function for PLwD when the intervention is delivered using a supervised placement model. Although strong evidence already exists for the efficacy of GREAT-CR, this is the first time that GREAT-CR will be evaluated in the context of trainee placements, and the first time a randomized *N*-of-1 design will be employed in a GREAT-CR study. We will determine whether goal attainment can be achieved as demonstrated in prior research when using our proposed delivery model. The intervention will be offered to approximately thirty-six PLwD, with outcomes evaluated at baseline, post-intervention and follow-up, and will include an embedded randomized *N*-of-1 single-case experimental design (SCED). *N*-of-1 or SCEDs a feature prominently in intervention literature [17]. Well-designed SCEDs can establish cause-effect relationships between interventions and outcomes [18] and are methodologically rigorous in evaluating intervention approaches [19]. The Oxford Centre for Evidence-Based Medicine ranks randomized *N*-of-1 designs as providing Level 1 evidence for intervention effectiveness [20], similar to reviews of RCTs [17]. This experimental method is recognized as especially important for optimizing personalized intervention approaches [21].

The second phase of the research will assess the effectiveness of the implementation model using an implementation-science approach. Implementation science is focused on identifying factors that impact on the uptake of interventions as part of routine care, rather than focusing on the effectiveness of the intervention itself, with the aim to enhance the availability and public health impact of evidence-based interventions [22]. The strategy for the proposed pilot is developed using the GREAT-iP (Goal-oriented Cognitive Rehabilitation in Early-stage Alzheimer’s and related dementias: a multi-center single-blind randomized controlled Trial into Practice) implementation framework [23]. This was designed to support widespread implementation of CR into service provision for people with early-stage dementia. An implementation study involving 14 UK-based organizations demonstrated that this framework is effective in supporting the delivery of CR in routine services [23]. Qualitative and quantitative data will be collected at organizational, practitioner, and service-user level to evaluate the feasibility, acceptability, appropriateness, and potential sustainability of the implementation model. The design is informed by recommendations for mixed and qualitative methodologies in implementation science [22], which suggest that deductive, positivist approaches, guided by the implementation framework, may be preferable to constructivist, exploratory, inductive paradigms [24]. Semi-structured interviews will be conducted with a sample of key stakeholders involved in the pilot study (see methods section). Framework analysis [25] will inform development of interview guides, data collection, and analysis. Quantitative indicators of implementation success will be derived by assessing outcomes against specified targets and analyzed descriptively to support the qualitative findings.

## Research aims

This pilot study addresses three key aims: (1) to investigate whether a supervised placement model can be effectively utilized within memory services to enhance the availability of GREAT-CR; (2) to explore the feasibility and acceptability of the proposed intervention delivery model for individuals with dementia, their families, trainee practitioners, and service providers; and (3) to examine the impact of GREAT-CR on goal attainment, cognitive function, and quality of life within the context of the supervised placements.

## Methods

The proposed research was approved by the St James’s Hospital and Tallaght University Hospital Joint Research Ethics Committee on the 27^th^ of May 2024. Reference number 2024-May-35703570. The protocol adheres to the Spirit guidelines [26,27]: see S1 Appendix. This pilot research involves two sub studies with five groups of research participants. Group 1, participants with dementia, will take part in both sub-study 1 and sub-study 2, while the remaining four groups will participate in sub-study 2. See Fig 1 for sub-study methodologies and participant groups.

**Fig 1 pone.0322121.g001:**
[figure not shown]
Flowchart of the pilot study protocol.

## Ethics declarations

Approval for all project research activities was obtained from the ethics committees at St James’ Hospital and Tallaght University Hospital Joint Research Ethics Committee. All data from participants will be stored in accordance with National College of Ireland and Tallaght University Hospital data protection and retention policies. For both sub-studies, participants will receive an information sheet and consent form at least one week prior to participation. The study will be explained in detail, including the phases of the intervention, the duration and number of sessions, as well as the measurements to be taken. Participants will also be informed about any potential risks associated with the study. Additionally, they will be provided with information regarding data protection, including how their data will be used, who will have access to it, how it will be stored, and their rights concerning their personal data. Participants will be informed that there will be no cost to them and that the study has received approval from the appropriate research ethics committee.

## Sub-study 1 – Cognitive rehabilitation intervention

### Participants

This study will include 36 participants with dementia, recruited through the Regional Specialist Memory Clinic (RSMC) at Tallaght University Hospital in Dublin, Ireland. Inclusion criteria specify that participants must have a diagnosis of early-stage dementia, exhibit mild-to-moderate cognitive impairment, be able to provide informed consent, and have a carer willing to provide support. Characteristics associated with positive outcomes in GREAT-CR trials [6] will also be considered for recruitment. These characteristics include being recently diagnosed, able to engage in daily activities and converse about them, motivated to reduce the impact of cognitive impairment on daily life, reasonably active, and supported by a carer who can encourage practice between sessions. Participants lacking the capacity to provide informed consent will be excluded from the research.

### Design and materials for sub-study 1

A quantitative pre-post design with and an embedded randomized *N*-of-1 SCED will be used. For all thirty-six participants, data on the primary outcome of goal attainment and satisfaction, and secondary outcomes of quality of life and cognition will be gathered at baseline, post intervention, and at a six-week follow-up. A subset of three participants will be randomly selected for the SCED analysis to evaluate the impact of GREAT-CR on objective measures of goal attainment. The SCED and reporting will adhere to the What Works Clearinghouse (WWC) Technical Documentation for SCDs [28] and the Single-Case Reporting Guideline in Behavioral Interventions [29]. A randomized multiple-baseline design will determine whether a causal relationship exists between the GREAT-CR intervention (independent variable) and the primary outcome of goal attainment (dependent variable). A multiple-baseline-across-participants approach will be utilized, where behavior on a specified goal will be assessed across three separate participants (e.g., [7]). We include both within-case (phase) randomization and start-point randomization [30]. As per WWC guidelines, an effect replication will be assessed across three participants, with three to five data points per phase (baseline and intervention). Interobserver agreement (IOA) will be collected by two independent assessors for each dependent variable.

### Measures/scales

Demographics and functional ability will be assessed at baseline. Demographic data will include age, gender, marital status, living status, level of education, and family carer demographics (see Table 1). Functional ability will be measured using the Functional Activities Questionnaire (FAQ) [31]. The FAQ evaluates participant’s ability to perform ten instrumental activities of daily living, for example “Writing checks, paying bills, balancing a cheque book”, which is indicative of functional independence in individuals with cognitive impairment. Six response options range from “Normal – I can do this by myself without difficulty” to “I need someone else to do this activity for me”. Responses are scored from zero to three with a higher score indicating lower levels of independent functioning.

**Table 1 pone.0322121.t001:** List of outcomes, measures and timepoints at which associated measures will be utilized.

Outcome	Measure	Timepoint
Participant Characteristics		
Demographic information	PLwD demographics: Age, gender, marital status, living status, level of education, self-rated health, time since dementia diagnosis, type of dementia.	Baseline
	Family carer demographics: Age, gender, level of education, relationship to PLwD, does the carer live with the participant (Y/N), average number of hours per week that care is provided to the participant.	
Functional ability	Functional Activities Questionnaire (self and carer rated)	Baseline
Primary Outcome		
Goal Attainment and Satisfaction (Subjective)	Bangor Goal Setting Interview (BGSI): Ratings (participant, family carer, practitioner) of current functioning related to each goal (1 – unable/not currently doing to 10 – able to do well with no difficulty) and current level of satisfaction with goal attainment (1- extremely dissatisfied to 10-extremely satisfied).	Baseline Post-Intervention Follow-Up
Goal Attainment (Objective)^*^	Practitioner-recorded proportion of correct responses/percentage goal attainment when practicing selected goal (see Kelly et al., 2019 for an example).	Baseline Each intervention session Post-intervention Follow-up
Secondary Outcomes		
Cognitive Function	Montreal Cognitive Assessment (MoCA)	Baseline Post-Intervention Follow Up
Quality of Life	Quality of Life in Alzheimer’s Disease (QoL-AD)	Baseline Post-Intervention Follow Up

*Measure will be collected only for SCD participants (n=3)

Our primary outcomes of interest, goal attainment and satisfaction, will be assessed using the Bangor Goal Setting Interview (BGSI) [11]. This semi-structured interview-based tool is designed to set and evaluate personalized goals for individuals with cognitive impairment [2]. Once goals have been identified, the PLwD’s current level of goal attainment will be assessed on a 10-point Likert scale from 1 “cannot do or am not doing successfully” to 10 “can do and am doing very successfully” and is rated by the participant, the carer and the practitioner. Participants also rate their satisfaction with their current level of goal attainment on a 10-point Likert scale from 1 “extremely dissatisfied” to 10 “extremely satisfied”. These outcomes will be assessed at baseline, post-intervention and at follow-up.

Secondary outcomes of cognitive function and quality of life will be assessed using the Montreal Cognitive Assessment (MoCA) [32] and the Quality of Life in Alzheimer’s Disease (QoL-AD) [33], and will be assessed at baseline, post-intervention and at follow-up (see Table 1). The MoCA is a brief screening instrument for dementia used with individuals who may experience cognitive difficulties [34]. The MoCA assesses cognitive domains comprising visuospatial/executive, naming, memory, attention, language, abstraction and orientation. The test has a maximum score of 30. A cut-off score of 26 is recommended by the test developers with a score below 26 being considered indicative of cognitive impairment; one point is added to the total score if the person has 12 years or less of formal education [32]. It has been previously suggested that this cut-off score of 26 has poor specificity meaning there may be a risk of misclassifying cognitively able people as having impairment [35]. In the Irish context, population-specific norms have been developed which are stratified according to age and education level which combats this criticism [36]. These normative data will be used in the current study rather than the cut-off score recommended by the test developers.

The QoL-AD is a self and proxy-rater measure that assesses quality of life (e.g., physical health, energy, mood, living situation, memory, family, marriage, friends, etc.) [33]. The QoL-AD is composed of 13 questions, with a factorial structure comprising three dimensions: physical, social, and psychological well-being. The total score ranges from 13 to 52, with each question rated on a 4-point Likert scale ranging from “Poor” to “Excellent”. A high score indicates a higher quality of life [33,37].

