#### Phase 1: Pre-intervention (Baseline) assessments and goal identification.

The first visit from the placement practitioner will provide an opportunity for the participant to ask questions, and for the practitioner to explain the study procedures and expectations again. If the participant agrees to continue, written informed consent will be obtained. The practitioner will gather baseline data (see Table 1 for list of baseline measures) and discuss possible goals. The first session would be expected to last around 90 minutes. Goal identification can take some time so may occur during the initial visit or in a subsequent visit. The placement practitioner will assist participants and their caregivers in identifying up to three personalized rehabilitation goals using the BGSI. Once goals are identified, the practitioners will work with the participant to operationally define the goals to ensure they are specific, measurable, achievable, relevant and time-oriented (SMART). Practitioners will subsequently work with their clinical supervisors to develop the intervention and session plans, and to determine how best to measure goal performance within sessions.

For the embedded N-of-1 design, baseline data on goal performance will be objectively measured (e.g., proportion of correct responses on a face-name recall goal) with baseline data monitored across three participants concurrently. The participants will be randomly assigned to different baseline durations (see Table 2 for an example). This allows for causal inferences by applying the intervention sequentially to each. An effect replication will be assessed across participants with at least 3–5 data-points per phase.

**Table 2 pone.0322121.t002:** Sample plan for the N-of-1 design showing random allocation of participants to predetermined baseline lengths and random allocation of intervention start-points from a possible two.

Participant # (randomly allocated)	Possible # baseline data points	Possible intervention start points	Actual design – *determined by ExPRT start point randomizer*
3	3/4	4/5	AAAABBBBBBBB
1	5/6	6/7	AAAAABBBBBBB
2	7/8	8/9	AAAAAAABBBBB

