#### Phase 2: Intervention.

The intervention will be tailored to each participant’s goals, utilizing techniques from the cognitive rehabilitation literature. The intervention will span approximately six to eight weeks with weekly 60–90-minute sessions, conducted at the participant’s home unless otherwise preferred (option available to conduct sessions in the Memory Clinic). The end of each session will include a review with the caregiver and planning for home practice. Rehabilitative approaches may include compensatory or restorative strategies. Compensatory strategies may include environmental or task modifications, practicing the use of memory aids like diaries, calendars, or medication reminders, or other techniques tailored to the participant’s needs like relaxation. Restorative strategies to support new learning or relearning of functional skills/information may incorporate task analysis, chaining, prompting and fading, multiple exemplar training, mnemonics, errorless learning and/or spaced retrieval. Strategies used during sessions will be documented weekly, and participants will receive a summary report at the end of the intervention. Practitioners will monitor participant’s progress on selected goals during each session to ensure intervention efficacy. For the N-of-1 participants, the intervention start-point will be predetermined (see Table 2) for their goals. The intervention is due to span six to eight weeks but for goals with longer baseline phases this may be less. Intervention length will be determined by participant need, availability and consent to work on goals.

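### The objective N-of-1 outcome is scored during practice, with no rule that scoring be unprompted or alike in both phases, so in-session assistance can pass for a treatment effect

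*Protocol article*

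**What the plan says.** Table 1 (Measures/scales) gives the objective goal-attainment measure, collected only for the three N-of-1 participants, as "Practitioner-recorded proportion of correct responses/percentage goal attainment when practicing selected goal". Its timepoints are "Baseline Each intervention session Post-intervention Follow-up". The table points to an earlier published study as an example of the measure.

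Phase 1 of the Procedure says that "baseline data on goal performance will be objectively measured (e.g., proportion of correct responses on a face-name recall goal" and so on. It also has practitioners work with their supervisors "to determine how best to measure goal performance within sessions".

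Phase 2 says that restorative strategies "may incorporate task analysis, chaining, prompting and fading, multiple exemplar training, mnemonics, errorless learning and/or spaced retrieval". It lists compensatory strategies, such as memory aids and task modification, separately. It adds: "Practitioners will monitor participant’s progress on selected goals during each session to ensure intervention efficacy".

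On the use of the measure, Design and materials for sub-study 1 states: "A randomized multiple-baseline design will determine whether a causal relationship exists between the GREAT-CR intervention" and goal attainment. As a safeguard, the same section says: "Interobserver agreement (IOA) will be collected by two independent assessors for each dependent variable". The Proposed analytic approach then compares phases by visual analysis (level, trend, variability, immediacy, non-overlap) and by a randomization test on mean phase differences.

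**The concern.** A baseline-versus-intervention contrast can be read as an effect on goal attainment only if goal attainment is measured the same way in both phases. Table 1 ties the measurement to practising the goal. In intervention sessions, practice may include prompts, or techniques meant to prevent errors. In baseline those techniques have not yet been introduced. Followed literally, the condition of measurement can change at the same session as the phase.

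This matters because the N-of-1 component is the only controlled comparison in sub-study 1. The results of the 36 participants are uncontrolled pre-post scores summarised descriptively, so the causal claim rests on this measure. An abrupt step at the start-point is what both the visual analysis and the test look for. A step produced by assistance would look like a step produced by learning.

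**Working it through.** **1. What the contrast estimates.** Let unaided accuracy in baseline be *p*, the true gain from learning *g*, and the lift from in-session assistance *h*.

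- Expected score in phase A: *p*
- Expected score in phase B: *p + g + h*
- Expected B minus A: *g + h*

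Only the sum is observed. If *g* = 0, the contrast still equals *h*. The contrast isolates *g* only if *h* = 0, which means scoring under the same unassisted conditions in both phases. No section of the article states this condition.

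**2. Whether a stated safeguard separates *g* from *h*.**

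- *Interobserver agreement* checks that two people record a response alike. Both can agree fully on a response that was prompted.
- *Start-point randomization* protects against time trends and coincident events. Assistance begins at the randomized start-point itself, so it moves with the phase under any randomization.
- *Supervisor-agreed measurement* is set for each participant without a common rule, so scoring may also differ between the three tiers.
- *Post-intervention and follow-up points* could show a prompt-driven lift falling away, but only if those points are unaided. The article does not say that they are.

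**3. The plan's own significance rule.** There are three tiers, two start-points per tier, and random allocation of participants to tiers.

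- Possible outcomes: 3! × 2³ = 6 × 8 = 48
- Rank 1: 1/48 = 0.0208
- Rank 2: 2/48 = 0.0417 (≤ .05)
- Rank 3: 3/48 = 0.0625 (> .05)

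The statement that the two most extreme outcomes are significant at .05 is reproduced.

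**4. Illustration of what a lift would do.** Inputs from the article:

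- three participants
- 12 data points each, and possible baseline lengths of 3/4, 5/6 and 7/8 (Table 2, which is labelled a sample plan)
- the rule of the two most extreme of 48

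Assumed, because the article gives no values:

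- unaided accuracy of 20%, 30% or 40%, constant throughout (*g* = 0)
- 5, 10 or 20 trials per session, with binomial scores
- a lift *h* that is immediate, the same for all three participants, and constant over phase B (no fading)

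The statistic is the average over participants of (mean of B − mean of A). With 20,000 runs per setting, the table shows the share of significant results. Ranges run over the three accuracies.

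| Lift *h* (points) | 5 trials | 10 trials | 20 trials |
|---|---|---|---|
| 0 | 4% | 4% | 4% |
| 10 | 12–14% | 17–20% | 26–31% |
| 20 | 27–30% | 41–46% | 63–70% |
| 30 | 46–49% | 68–71% | 87–90% |
| 40 | 66–68% | 86–88% | 97% |

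A separate run of 4,000 replicates, with 10 trials and accuracy going from 40% to 70%, gave 67%. The range for a 30-point lift at 10 trials is therefore about 67–71%. With no lift the test holds its nominal 2/48.

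**The case against.** The strongest reply is that the phrase in Table 1 is ambiguous and the concern takes its worst reading. One definition serves four timepoints, and three of them lie outside the intervention sessions, so practising may mean no more than attempting the goal, scored the same way throughout. Phase 1's recall example fits that. The restorative techniques are optional, and prompting is paired with fading. Nothing says that a prompted response counts as correct. Scoring is left to individual goal definitions, to a cited example and to single-case standards that the article adopts, and an article need not spell out every probe. For compensatory goals, success with the aid is the intended effect. The simulation puts in a lift and then finds it.

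Much of this stands. A reader might infer that prompting necessarily inflates the intervention-phase score, or that the phase difference cannot measure goal attainment on any reading. The documents support neither: they allow assisted scoring but do not prescribe it, and the neutral reading is available. The percentages show how the test responds to an assumed lift, not how likely a lift is.

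What does not stand is that this is only omitted detail. Table 1 states a measurement condition, and that condition is open to bias in the sessions where assistance is allowed. The cited study is offered as an example and not as a scoring rule.

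**Conclusion.** The concern holds in a limited form. As worded, the objective outcome can be scored under assistance in the intervention phase and without it in baseline. For restorative goals, assistance can then produce a phase difference with no learning behind it, and the stated safeguards would not reveal this. Under the assumptions above (10 trials, 20–40% unaided accuracy, constant lift, no fading), a 10-point lift gives about 17–20% significant results and a 30-point lift about 67–71%, against about 4% with none. Fading would make the lift shrink over the phase, and that was not modelled.

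The point concerns three participants and the causal claim of sub-study 1. A reader might extend it to the whole sub-study, but the BGSI, MoCA and QoL-AD results of the 36 are not scored this way, and the aims on the delivery model do not depend on it. It should be fixed. Confidence is medium, because the scoring convention actually intended is not shown.

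**What to change.** In Table 1, replace the closing reference to practising the goal with wording such as: *on an unprompted probe of the selected goal, taken at the start of each baseline and intervention session and at post-intervention and follow-up, before any practice, prompting or feedback, with the same items and conditions in both phases; prompted responses are not scored as correct.* Carry the same rule into Phases 1 and 2 of the Procedure. Allow an aid during the probe only where the operational goal is defined as performance with that aid. Keep in-practice scores for monitoring, outside the phase comparison.

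The cost is a few minutes per session for three participants and a short text change. Gains on unprompted probes may look smaller or appear later than practice scores. The rule has to be in place before data are collected, because unprompted scores cannot be recovered from prompted ones.
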